#### Sample size calculation

Mean effect sizes of current interventions on social functioning are around *d* = 0.5 [52]. With the G-power software package, the effect size is calculated based on an estimated effect size on the primary outcome of 0.5 [13, 53, 54], two groups, statistical power of 0.8, alpha of 0.05 and a standard deviation of 0.9. The required sample size of 102, with a correction for an estimated 13% [55] drop-out, amounts to *N* = 116.

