**Methods:**

A total of 116 participants (age 18–40) with a DSM-5 diagnosis of schizophrenia spectrum or other psychotic disorder and problems with social functioning will be recruited from mental healthcare institutes in the Netherlands. Participants will be randomized to the experimental condition (VR-SOAP) or active VR control condition (VRelax). VR-SOAP consists of 14 sessions and 5 modules addressing causes of impaired social functioning: four optional modules (1–4) and one fixed module (5). Vrelax consists of 14 sessions that entail psychoeducation, stress management, relaxation techniques, and the exploration of relaxing environments in VR. Primary outcomes are quantity and quality of social contacts, leisure activities and social participation, measured with the experience sampling method (ESM). Secondary outcomes are psychiatric symptoms, social behaviour, social cognition, self-esteem, self-stigma and paranoid thoughts. Treatment effects will be compared at pre-treatment (baseline), post-treatment and at 6-month follow-up.

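### The required N of 102 mixes a cited d of 0.5 with an SD of 0.9 and states no sidedness; a two-sided 0.05 test at d = 0.5 would have about 70% power, not 80%

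*Protocol article*

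**What the plan says.** Under Sample size calculation, the protocol article first gives its rationale: "Mean effect sizes of current interventions on social functioning are around" d = 0.5. It then names the G-power package and lists its inputs: "an estimated effect size on the primary outcome of 0.5 [13, 53, 54], two groups, statistical power of 0.8, alpha of 0.05", with the last of these continuing as "alpha of 0.05 and a standard deviation of 0.9". The result follows: "The required sample size of 102, with a correction for an estimated 13% [55] drop-out, amounts to" N = 116. The Methods part of the abstract repeats the total ("A total of 116 participants"). The Randomization section fixes 1:1 allocation. Nowhere does the article say whether testing is one- or two-sided, and the sample size paragraph does not name the test used in the calculation.

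**The concern.** A standardized effect size needs no standard deviation, so giving both leaves it unclear which effect the trial was sized for. If 0.5 is the standardized d that the cited literature supports, the usual two-sided calculation gives a clearly larger number than 102. If 0.5 is a raw difference to be divided by 0.9, the trial was sized for an effect larger than the one cited.

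What is at stake is how the result is read. On the paragraph as written, a null result would be taken to have a 20% chance of missing d = 0.5. Under a two-sided 0.05 test that chance is nearer 30%. The drop-out step also looks wrong: it multiplies by 1.13 where it should divide by 0.87.

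**Working it through.** **Inputs.** From Sample size calculation: effect 0.5, SD 0.9, power 0.80, alpha 0.05, required N 102, drop-out 13%, total 116. From Randomization: 1:1 allocation. Sidedness is not given, so both are tried. The comparison is an unadjusted two-group comparison of means.

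**Formulas.** Normal approximation: n per arm = 2(z_α + z_β)² / d², with z_β = 0.842 and z_α = 1.960 (two-sided) or 1.645 (one-sided). The t-test figures come from the noncentral t distribution.

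**Reproducing 102**

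| Reading of 0.5 | Sides | Normal approximation, total N | t-test, n per arm and total N | Power at 51 per arm (t / normal) |
|---|---|---|---|---|
| Standardized d = 0.5 | one | 100 | 50.2 → 51; **102** | 0.806 / 0.811 |
| Standardized d = 0.5 | two | 126 | 63.8 → 64; 128 | 0.706 / 0.714 |
| Raw 0.5, SD 0.9 (d = 0.5/0.9 = 0.556) | one | 82 | 40.8 → 41; 82 | 0.873 / 0.877 |
| Raw 0.5, SD 0.9 (d = 0.556) | two | **102** | 51.8 → 52; 104 | 0.793 / 0.801 |

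For example, the two-sided normal approximation at d = 0.556 is 2 × 7.849 × 0.81 / 0.25 = 50.9, so 51 per arm. At d = 0.5 it is 2 × 7.849 / 0.25 = 62.8, so 63 per arm.

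Two rows give exactly 102: one-sided at d = 0.5 by the t-test, and two-sided at d = 0.556 by the normal approximation (104 by the t-test). The row that combines the cited d = 0.5 with a two-sided test does not.

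**Drop-out**

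- As stated: 102 × 1.13 = 115.3, so 116.
- Check: 116 × 0.87 = 100.9 evaluable, below 102.
- Correct inflation: 102 / 0.87 = 117.2, so 118.
- Effect on two-sided power at d = 0.5: 0.706 at 51 per arm against 0.701 at 50.5 per arm.

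**What 116 supports under a two-sided 0.05 test.** With 50.5 per arm (116 less 13%), power is 0.701 at d = 0.5 and 0.796 at d = 0.56.

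**The case against.** The strongest reply is that 102 can be reached by an ordinary two-sided calculation that uses every stated input: a raw difference of 0.5, SD 0.9, alpha 0.05 and power 0.80 give 51 per arm by the normal approximation. The t-test answer of 104 differs by two participants and 0.7 points of power, too little to rule this reading out. The one-sided reading leaves the SD without a use, and no one-sided test is declared.

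This stands. A reader might infer that 102 can only have come from a one-sided test, and the article does not support that. The named package's t-test does return 102 for the one-sided case and 104 for the SD reading, but the article does not say which test was chosen.

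The reply does not remove the problem. If 0.5 is raw, the trial is sized for d = 0.556, and the cited d of about 0.5 does not support that input.

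A second reply is that the planned analysis is a mixed model with group-by-time terms, so t-test power is not the power of the final analysis. That is correct as far as it goes. The power of that model depends on within-person correlations that the article does not give. As an assumption only, baseline adjustment at 51 per arm and d = 0.5, two-sided, would give power of 75%, 82% or 94% for a baseline-outcome correlation of 0.3, 0.5 or 0.7. For a change-score contrast at a correlation of 0.5 there is no gain (70.6%). None of this can be credited to the stated calculation.

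**Conclusion.** The concern holds as an unresolved inconsistency in the sample size paragraph. The stated 80% power applies either to d = 0.5 under an undeclared one-sided test, or to d = 0.556 under a two-sided test. On neither reading does a two-sided 0.05 test have 80% power at the cited d = 0.5: power is 70.6% (t-test) or 71.4% (normal approximation) with 102 evaluable, and 128 evaluable participants would be needed (126 by the normal approximation).

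A reader might go further and conclude that the trial as designed has only 70% power. The article does not establish that. The figure is conditional on two-sided testing, on a true standardized effect of 0.5, and on an unadjusted two-group comparison.

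The drop-out error is certain but minor: two participants, and less than one point of power.

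**What to change.** Reword the sample size paragraph:

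1. State whether the primary test is one- or two-sided at 0.05. If it is one-sided, declare it.
2. Say whether 0.5 is a standardized d or a raw difference with SD 0.9. If it is standardized, drop the SD. If it is raw, state that the powered effect is d = 0.556 and justify that value.
3. If testing is two-sided, restate the result for an unadjusted two-group comparison, for example: *N = 116, about 101 evaluable after 13% drop-out, gives about 80% power for d = 0.56 and about 70% for d = 0.5.*
4. Correct the inflation to 102/0.87 = 118, or keep 116 and state about 101 evaluable.
5. If power from baseline adjustment is mentioned, label the correlation as an assumption and show a range.

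The cost is one paragraph, with no extra recruitment if 116 is kept. The downside is that, under two-sided testing, the stated power at d = 0.5 becomes less favourable.

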### Data management

Participant data will be pseudonymized using a study ID. Data will be captured and stored in the Redcap and Roqua database system within the protected servers from the UMCG. Personal data such as phone numbers or (email) addresses to contact the participants during the research period will be strictly separated from other research data and is only accessible to the researcher and research assistant(s). The delegation log records which individual holds which role in the study. After completing the research project (i.e. data collection, data analysis, and publication of articles with primary and secondary outcomes), all research data will be transferred to the UMCG Research Drive for long-term storage. Research data will be stored for 15 years after the data collection has been completed (i.e. last research assessment for the last patient has been performed) in accordance with the NFU guidelines for WMO-compliant research. This data will be stored in a study-specific folder and is initially only accessible to the PI. Third parties can submit a research proposal and data request to the PI. The PI evaluates if the request falls within the scope of the research question and informed consent. More information regarding data management can be requested from the PI.

### Adverse events

The study adheres to the Medical Ethics Committee’s guidelines [56] regarding adverse events, and all participants are insured in the event of any trial-related harm.

## Discussion

The primary objective of this study is to evaluate the effect of a novel, modular VR intervention for improving social interaction difficulties in people with a psychotic disorder. It is hypothesized that the VR-SOAP group will show greater improvements in the quantity and quality of social contacts, leisure activities and social participation than the VRelax group at post-treatment and follow-up and we expect that these improvements are mediated by changes in underlying processes.

Although NICE guidelines consider social functioning as one of the “critical” outcome measures, current approaches have shown only moderate effects to this end [11–13]. Given that in the Netherlands alone around 100,000 people are receiving treatment in a mental health care setting for a psychotic disorder, many of whom have problems with social interactions [57], more effective interventions to improve social functioning are highly needed.

If VR-SOAP proves to be effective, it provides young adults with a psychotic disorder much-needed support to engage in social activities and to participate in society. Additionally, since the treatment consists of multiple modules targeting different transdiagnostic factors this trial might provide input for new treatments to improve social functioning in a range of symptoms and disorders, e.g. mood, autism spectrum and anxiety disorders.

## Data Availability

Data will be stored in the clinical data system “RedCap” provided by the Trial Coordination Center of the University Medical Center Groningen. A data request form will be made available. Third parties can submit a data request form to the investigator.

## Abbreviations

VR-SOAP: Virtual Reality Treatment for Social Activities and Participation
ESM: Electronic sampling method
TAU: Treatment as usual
SFS: Social Functioning Scale
SIG: Schaal Interpersoonlijk Gedrag
SERS-SF: Self-Esteem Rating Scale Short-Form
SIAS: Social Interaction Anxiety Scale
ISMI: Internalized Stigma of Mental Illness Scale
DAQ: Dating and Assertion Questionnaire
R-GPTS: Revised Green et al. Persecutory and Paranoid Thought Scale
BLERT: Bell-Lysaker Emotion Recognition Task
BNSS: Brief Negative Symptom Scale
PANSS: Positive and Negative Syndrome Scale
IPC: I-group Presence Questionnaire
